**Memory recall**					
	Mnemonics (face-name recall)	Give a photograph of a relative. Generate a mnemonic after the discussion that will be used to assist recall. During the training phase, using the forward cueing method, increase the cues until the patient identifies the picture.	Run 1 training trial, then test immediately, and again after 30 seconds, 1 minute, 2 minutes, 5 minutes, and 10 minutes.		
	Cueing (number recall)	Generate mnemonics to remember phone numbers. During the training phase, prompt a line in increasing or decreasing order.	N/A^a^		
	Chunking (story recall)	Read a story in front of the patient. Break the story into parts and try to imagine the important key points, such as what, where, who, when, and why.	N/A		
	Method of loci (procedural memory and fluency training)	Prompting and fading, action-based encoding, chaining, and fluency training (names and numbers).	N/A		
	Spaced retrieval (semantic impairments)	Repeated rehearsal of word-picture pairing will improve the ability to name trained items for 4 people. For word association, the therapist will give a word and ask the patient to identify a related word with the same meaning.	N/A		
**Executive function**					
	Naming task	Ask the patient to say the name of any item. Show the item for 5 seconds, then repeat the task for 60 trials.	There were 60 trials in total, and the task lasted 5 minutes.		
	Calculation task	Ask the patient to add or subtract 2-digit numbers. The patient must respond within 5 seconds.	N/A		
	Stroop color-word task	The therapist shows words in different colored fonts. At times, the color matches the word itself, and at other times, it does not. The patient must name the color of the font.	N/A		
	Working memory task	Show the patient a series of numbers for 2 seconds. The patient should then repeat the series.	N/A		
**Attention**					
	Sustained and selective attention	Elemental training: focus on breathing and body-part awareness.	20 minutes of training		
	Alternating and divided attention	Functional training: make a grocery list to prepare meals, select the correct food pictures showing their expiry dates, and determine locations on the map.	N/A		
	Information processing	The perceive, recall, plan, and perform system [18]	N/A		
	Perceive	The patient decides which sensory information to attend to, then analyzes the characteristics of objects, surfaces, and body parts.	10 minutes of training		
	Recall	The patient will recall prior knowledge of the procedure and then apply the relevant knowledge required to perform the task.	N/A		
	Plan	The patient will think, prepare to perform, and make decisions to achieve the goal.	N/A		
	Perform	The therapist will analyze whether the patient is able to initiate and terminate the response, and to continue and persist as the task requires.	N/A		
**Physical fitness**					
	Aerobic exercises [18] (frequency, intensity, interval, and time principle)	Brisk walking, jogging, and static cycling	Frequency: 5-6 times per week; intensity: easy to moderate, approximately 60%-75% of maximum heart rate.		

^a^N/A: not applicable.

### Rationale

The rationale for including cognitive behavioral training in the control group intervention is based on its established effectiveness in addressing cognitive and behavioral disturbances, as demonstrated in several recent studies. Substantial evidence indicates that cognitive behavioral training significantly alleviates anxiety and depression among individuals diagnosed with cancer. Furthermore, a few studies have explored the role of cognitive behavioral training in reducing cancer-related fatigue. Consequently, cognitive behavioral training may serve as a promising approach to mitigating the adverse effects of chemotherapy [19]. A systematic review and meta-analysis further concluded that cognitive behavioral training, when combined with resistance and aerobic exercise, is more effective, as active exercise enhances physical capacity. In addition, cognitive behavioral training contributes to fatigue reduction by improving coping mechanisms for stress and promoting better activity management [20].

By targeting key domains such as attention, memory, processing speed, and executive function, neurocognitive exercises have been employed in an experimental study by Sundar et al [21] to aid cancer survivors in recovering from the cognitive effects of chemotherapy. Compared with aerobic exercises, neurocognitive training was found to produce significantly greater improvements in both cognitive function and overall quality of life. The study further demonstrated that enhancements in cognitive performance among postchemotherapy cancer survivors are strongly correlated with domain-specific cognitive training [21].

### Outcome Measures

#### Primary Outcomes

##### Mini-Mental State Examination

The MMSE comprises 11 questions designed to assess cognitive performance across 5 domains: orientation, registration, attention and calculation, recall, and language. Developed in 1975, the MMSE has a maximum score of 30 points. A total score of 23 or below indicates cognitive impairment, whereas a score of 24 or above is considered within the normal range.

##### Montreal Cognitive Assessment

According to clinicians, the MMSE takes approximately 10 minutes to administer. It assesses various domains of cognition, including visuospatial skills, executive functions, attention, concentration, calculation, language, abstraction, memory, and orientation.

##### Functional Assessment of Cancer Therapy—Cognitive

The Functional Assessment of Cancer Therapy—Cognitive Function version 3 is a 27-item self-report questionnaire designed to assess cognitive concerns among patients with cancer. It comprises 4 subscales, including Physical well-being, Social/family well-being, emotional well-being, and Functional well-being.

#### Secondary Outcomes

##### European Organisation for Research and Treatment of Cancer Quality of Life Questionnaire Core 30

The European Organisation for Research and Treatment of Cancer Quality of Life Questionnaire (EORTC QLQ-C30, version 3) is a 30-item instrument specifically developed to assess health-related quality of life in patients with cancer.

##### Patient-Specific Functional Scale

The Patient-Specific Functional Scale is a self-reported, patient-centered tool used to evaluate functional changes over time. Developed by Stratford and colleagues [22], the scale serves as a versatile measure of function that can be applied to individuals with varying levels of independence.

#### Sample Size Calculation

Calculation of sample size by Cohen effect size by comparing 2 means:

Effect size (d) = (μ_2_ – μ_1_)/σ = 0.8 (estimated)

Considering a large effect size difference of 0.8, the sample size is calculated as follows:

N=([1 + r]/r)([Z_1–α/2_ + Z_1–β_]^2^/d^2^) + (Z^2^_1–α/2_)/2(1 + r)

where *Z*_1–α/2_ at the 5% level of significance = 1.96; *Z*_1–β_ at 80% power = 0.84; ratio allocation (group 2/group 1) = 1.

Sample size (n) = ([1 + 1]/1)([1.96 + 0.84]^2^/0.8^2^) + (1.96)^2^/2(1 + 1) = 26 per group.

Considering a 15% dropout (n=4), a total of 30 samples are required per group.

### Sample Size

The sample size calculation used the Cohen *d* formula to compare 2 means. The effect size (*d*) was estimated using the following equation:

Effect size = *d* = (*μ*_2_ – *μ*_1_)/*σ* = 0.8

Given a large effect size (*d*=0.8), the required sample size per group was determined using the following formula:

*N*=([1 + *r*]/*r*)([*Z*_1–α/2_ + *Z*_1–β_]^2^/*d*^2^) + (*Z*^2^_1–α/2_)/2(1 + *r*)

where *Z*_1–α/2_ at the 5% level of significance = 1.96; *Z*_1–β_ at 80% power = 0.84; ratio allocation (group 2/group 1) = 1.

Substituting these values:

n=([1 + 1]/1)([1.96 + 0.84]^2^/0.8^2^ + (1.96)^2^/2(1 + 1)

n=2×([2.8]^2^/[0.64])+(3.84/4)

n=2 × (7.84/0.64) + 0.96

n=2 × 12.25 + 0.96

n=24.5 + 0.96= 25.46

Rounding up, 26 participants per group are required. Considering a 15% dropout rate (approximately 4 participants per group), the final sample size will be 30 participants per group, totaling 60 participants for the study.

### Safety Outcomes

Adverse events will be reported as they occur. No negative effects are expected.

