### Selection of Participants

After obtaining ethical clearance from the Institutional Ethics Committee, patients diagnosed with cancer and scheduled to undergo chemotherapy will be identified at Siddharth Gupta Memorial Cancer Hospital. Permission will be sought from the treating residents, and eligible patients who meet the inclusion criteria will be enrolled after obtaining informed consent. Treatment will commence within 1 week of initiating the chemotherapeutic agent, and baseline data will be recorded. Participants will receive cognitive rehabilitation focusing on memory, attention, information processing, and executive function, with the aim of enhancing cognitive performance and improving quality of life. The first outcome measure, the Mini-Mental State Examination (MMSE), will be administered before the initiation of chemotherapy along with baseline data to assess cognitive function. Subsequently, the Montreal Cognitive Assessment will be conducted over 4 chemotherapy cycles. Participants will undergo the intervention 5 days per week, and following the completion of the 4 chemotherapy cycles, postintervention baseline data will be recorded. The outcome measures will be used to assess the degree of cognitive impairment. Follow-up assessments will be conducted after each chemotherapy cycle and weekly after completion of the intervention. Baseline outcome measures will be recorded after 4 chemotherapy cycles, and follow-up evaluations will be carried out once a week for 4 consecutive weeks.

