### Control Group

Participants will perform aerobic exercises and cognitive behavioral training daily. The program will include brisk walking, cycling, jogging, and cognitive skill activities for 45 minutes per day, 5 days a week, over 4 weeks. These activities will not require direct supervision.

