#### Monitoring Harms

Every instance of an adverse event will be reported to the Ethics Committee and the clinician responsible for evaluating and managing both anticipated and unanticipated adverse events, as well as any other unforeseen consequences arising from the trial interventions or trial conduct.

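### As-it-occurs adverse-event reporting, with therapist-delivered sessions in one arm and unsupervised activities in the other, can make recorded events differ by arm without a true difference in safety

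*Protocol article*

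**What the plan says.** **Collection.** Protocol article, Safety Outcomes, complete text: "Adverse events will be reported as they occur. No negative effects are expected."

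**Onward reporting.** Monitoring Harms says where an event goes once it is known: "Every instance of an adverse event will be reported to the Ethics Committee and the clinician responsible for evaluating and managing" it. The same sentence covers anticipated as well as unanticipated events.

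**Control arm.** Control Group prescribes "brisk walking, cycling, jogging, and cognitive skill activities for 45 minutes per day, 5 days a week, over 4 weeks", and adds: "These activities will not require direct supervision."

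**Intervention arm.** Table 2 gives a therapist an active part in several cognitive tasks. Under executive function: "The therapist shows words in different colored fonts." Under information processing: "The therapist will analyze whether the patient is able to initiate and terminate the response." The arm also has an aerobic component, "Brisk walking, jogging, and static cycling", for which supervision is not stated either way.

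**Contacts.** Selection of Participants states: "Follow-up assessments will be conducted after each chemotherapy cycle and weekly after completion of the intervention." It describes these contacts in terms of outcome measures and does not limit them to one arm. Trial Design and Participant Timeline describe only an assessment before the 4-week intervention and one after it.

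**The concern.** When the only stated rule is to report events as they occur, the chance that an event is recorded depends on whether someone sees it or the participant mentions it. The two arms appear to differ on this by design. A participant working through tasks with a therapist has a natural occasion to mention dizziness, distress or a fall. A participant exercising alone has to remember the event and raise it later.

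The population sharpens the point. Inclusion Criteria require grade I or II cognitive impairment, and the Introduction lists working and short-term memory among the deficits.

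Two things are at stake. Any listing of events by arm can show an excess in the rehabilitation arm that reflects observation and not harm. And a real problem in the less observed arm, whose participants exercise during chemotherapy, can go unrecorded. There will be background events for unequal capture to act on: Statistical Analysis itself allows for participants who die from adverse effects of chemotherapy.

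**Working it through.** **1. Does any section supply a common method of finding events?**

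| Section | What it settles | Same method of finding events in both arms? |
|---|---|---|
| Safety Outcomes | events reported as they occur | not stated |
| Monitoring Harms | who receives a reported event | not stated |
| Selection of Participants | assessments after each cycle and weekly afterwards | contacts exist, but no adverse-event enquiry is tied to them |
| Control Group | no direct supervision needed | less opportunity to observe |
| Table 2 | therapist delivers or observes several cognitive tasks | more opportunity to observe |

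The article thus fixes a reporting rule that depends on contact, and fixes contact that differs by arm.

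**2. Arm size.** The only figure taken from the plan is 30 per group. It reproduces from Sample Size: 2 × (1.96 + 0.84)² / 0.8² + 1.96² / 4 = 24.5 + 0.96 = 25.46, rounded up to 26; then 26 × 1.15 = 29.9, so 30. Nothing below turns on how this was derived.

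**3. Illustration.** The article gives no adverse-event rate and no capture probability, so both are assumed here. Let p be the true risk, equal in both arms, s₁ the probability that an event is recorded in the intervention arm and s₀ that in the control arm.

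- Expected participants with a recorded event: 30 × p × s
- Apparent risk ratio: (p × s₁) / (p × s₀) = s₁ / s₀, whatever p is

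With s₁ = 0.9:

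| True risk p | s₀ = 0.9 | s₀ = 0.7 | s₀ = 0.5 |
|---|---|---|---|
| 10% | 2.7 vs 2.7 | 2.7 vs 2.1 | 2.7 vs 1.5 |
| 20% | 5.4 vs 5.4 | 5.4 vs 4.2 | 5.4 vs 3.0 |
| 30% | 8.1 vs 8.1 | 8.1 vs 6.3 | 8.1 vs 4.5 |
| **Apparent ratio** | **1.00** | **1.29** | **1.80** |

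**4. The reverse case.** Unequal capture can also hide a true excess in the control arm. With 90% and 50% capture, true risks of 20% (intervention) and 36% (control) give 30 × 0.20 × 0.9 = 5.4 and 30 × 0.36 × 0.5 = 5.4 recorded. The arms look alike although the true control risk is 0.36 / 0.20 = 1.8 times as high.

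**5. After the fix.** If events are sought identically in both arms, s₁ = s₀ can be expected for the elicited events and the ratio returns to 1.00 when true risks are equal.

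**The case against.** The strongest reply is that the Safety Outcomes sentence is about timing, not method. It does not say that participants will never be asked, and enquiry scripts and forms are details an article commonly leaves to the full protocol. That is fair as far as it goes: a missing form would be no finding. What remains is that the article has a dedicated safety section, states one rule there, and elsewhere fixes unequal contact. Following those statements as written can give unequal capture, and Monitoring Harms does not help because it begins once an event is known.

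A reader might infer several stronger things that the article does not support:

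- **That counts will differ, or that rehabilitation will look less safe.** This depends on capture rates that are not given. The ratios above simply restate the assumed rates.
- **That a planned safety comparison is biased.** Statistical Analysis specifies no between-arm test of adverse events; its chi-square analysis is for efficacy. The concern applies to any by-arm listing and to noticing harm at all.
- **That intervention participants have 20 therapist contacts (5 days × 4 weeks) against none for control.** No section says a therapist attends every session, many Table 2 tasks do not mention one, and activities that need no direct supervision are not the same as no staff contact.
- **That exercise-related events are better observed in the intervention arm.** Its aerobic component is of the same kind as the control arm's, and its supervision is not stated. The contrast rests on the cognitive sessions, where a participant has an occasion to mention an event.

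It is also true that counts this small settle little: 5 against 3 events among 30 per arm gives a Fisher exact p of 0.71. This limits any safety conclusion but does not justify collecting events differently in the two arms.

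**Conclusion.** The point holds in a limited form. Under the stated rule and the stated difference in contact, recorded adverse events can differ by arm without a true difference in safety, and events in the less observed arm can be missed. The direction that the design suggests is under-recording in the control arm. The size is unknown. An apparent ratio of 1.3 to 1.8 follows only from assumed capture of 90% against 70% or 50%, and equal capture gives 1.0. No efficacy result and no sample-size figure is affected. The change is worth making because it is specific and cheap, and serves better than the present rule.

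There is also a smaller inconsistency: Safety Outcomes expects no negative effects, whereas Monitoring Harms provides for anticipated adverse events.

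**What to change.** In Safety Outcomes:

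1. Add one identical, scripted adverse-event enquiry for both arms at the assessments both already attend: after each chemotherapy cycle, at the post-intervention assessment, and at the weekly follow-ups. The schedule in Selection of Participants must first be reconciled with Trial Design and Participant Timeline, which show only assessments before and after the 4 weeks. The weekly follow-ups come after the intervention ends, so during the intervention itself the enquiry relies on the cycle assessments.
2. Grade events with the National Cancer Institute criteria already used for eligibility.
3. Keep reporting every event as it occurs, and report all events by arm. Mark how each was found: common enquiry, or therapist session or spontaneous report. Any between-arm comparison can then use the commonly elicited events without dropping the others. Restricting the safety table to elicited events alone could hide harms that a therapist saw directly.
4. Delete the second sentence of Safety Outcomes or reconcile it with Monitoring Harms.

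**Cost.** One short form and a few minutes per visit. No new visits are needed if the reconciled schedule keeps those in Selection of Participants. More minor chemotherapy events will be recorded. Results gives data collection as November 14, 2024 to November 14, 2025. If collection has ended, the unequal opportunity to record events should be declared as a limitation when safety is reported.

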### Statistical Analysis

For demographic factors, all data will be summarized using baseline characteristics, expressed as the mean and SD for continuous data and as frequency and percentage for categorical data.

The analysis of outcome variables will primarily focus on continuous variables. For parametric data, the minimum, maximum, mean, SD, SE, and 95% CI will be summarized. The normality of continuous outcome variables will first be tested using the Kolmogorov-Smirnov test at a 5% level of significance (*P*≤.05). If the data are found to deviate from normality, a nonparametric test will be applied to determine significance. An independent *t* test will be conducted for group comparisons to assess significant differences at the 5% level (*P*≤.05). The intervention groups will receive (1) cognitive training supplementing traditional physical treatment and (2) traditional physical treatment.

The effect size at different assessment visits between the 2 groups will be calculated for the variables MMSE and Montreal Cognitive Assessment. For nonnormal data, descriptive statistics will include the mean, median, and lower and upper quartiles. The Mann-Whitney test will be applied to determine statistical significance when nonparametric methods are required.

Categorical variables will be summarized using frequency (n) and percentage. Chi-square analysis will be performed to evaluate efficacy across categorical variables. An intention-to-treat analysis will be applied to minimize attrition bias among participants, including those lost to follow-up or deceased due to adverse effects of chemotherapeutic drugs.

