**Figure 1 figure1:**
[figure not shown]
CONSORT (Consolidated Standards of Reporting Trials) flow diagram.

Descriptive statistics will be used to analyze demographic variables such as age and gender. Measures including mean, SD, frequency (n, %), chi-square test, and independent *t* test will be applied to confirm the homogeneity of descriptive statistics. Inferential statistics between the 2 groups will be assessed using an unpaired (2-tailed) *t* test. All statistical analyses will be performed using SPSS software, version 21.0 (IBM Corp). For this study, a *P* value of less than .05 will be considered statistically significant.

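### Three unranked primary outcomes are each tested at 5%, while the sample size covers one unnamed 5% comparison

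*Protocol article*

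**What the plan says.** Under Primary Outcomes the protocol article describes three instruments:

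- the MMSE ("The MMSE comprises 11 questions designed to assess cognitive performance across 5 domains");
- the "Montreal Cognitive Assessment";
- FACT-Cognitive, which "is a 27-item self-report questionnaire designed to assess cognitive concerns among patients with cancer".

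Secondary Outcomes start only after these, with the EORTC questionnaire.

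The Statistical Analysis section states that an independent t test "will be conducted for group comparisons to assess significant differences at the 5% level", with Mann-Whitney as the nonparametric alternative. The text after Figure 1 makes the t test two-tailed and sets one threshold for the whole study: a P "value of less than .05 will be considered statistically significant". No section ranks the three scales, orders their tests, divides alpha or requires all three to succeed.

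The sample size sections use a single standardised difference: "Considering a large effect size difference of 0.8, the sample size is calculated as follows". The inputs are 1.96 for 5% significance, 0.84 for 80% power and 1:1 allocation. They give 26 per group, raised to 30 for 15% dropout. Neither section names the outcome to which d = 0.8 applies.

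**The concern.** The article fixes three things that do not fit together: three primary outcomes, a 5% threshold for each comparison, and a sample size for one comparison. Because no decision rule is given, a reader cannot tell what result would make the trial positive.

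- If any one significant scale suffices, the false-positive risk for the trial exceeds 5%.
- If alpha is later divided to prevent this, the stated 80% no longer holds for each outcome.
- If all three must succeed, the 5% is safe but the power falls short.

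The stake is practical. The article says in advance that it expects significant results, and with three unranked primaries whichever scale falls below .05 can become the headline.

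**Working it through.** **Inputs from the protocol article.** Three primary outcomes (Primary Outcomes); two-sided 5% per comparison (Statistical Analysis; text after Figure 1); z values 1.96 and 0.84, d = 0.8, 1:1 allocation, 26 evaluable and 30 enrolled per group, 15% dropout (Sample Size Calculation; Sample Size). The correlation between the three scales is not given, so a range is assumed.

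**1. The plan's own figure.** n = 2 × (1.96 + 0.84)² / 0.8² + 1.96² / 4 = 24.5 + 0.96 = 25.46, so 26 per group. Adding 15% (26 × 0.15 = 3.9, about 4) gives 30. The figure reproduces. With the noncentral t distribution, 26 per group gives 80.7% power at two-sided 5%. The calculation is right for one test.

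**2. Familywise error if any one success counts.** For independent outcomes: 1 − 0.95³ = 1 − 0.857 = 14.3%. For equally correlated normal test statistics, the chance that at least one exceeds 1.96 in absolute value is:

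| Assumed correlation | Familywise error |
|---|---|
| 0 | 14.3% |
| 0.3 | 13.6% |
| 0.5 | 12.5% |
| 0.7 | 10.9% |
| 0.9 | 8.4% |

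This is 1.7 to 2.9 times the 5% level (8.4/5 and 14.3/5).

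**3. Power per outcome under Bonferroni.** Alpha becomes 0.05/3 = 0.0167. At d = 0.8, with the noncentral t distribution:

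| Per group | Alpha 0.05 | Alpha 0.0167 |
|---|---|---|
| 26 | 80.7% | 65.8% |
| 30 (no dropout) | 86.1% | 73.5% |

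At 26 per group, the difference detectable with 80% power rises from d = 0.79 to d = 0.92.

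**4. Size needed to restore 80% per outcome at 0.0167.** The normal critical value is 2.394. The plan's formula gives 2 × (2.394 + 0.84)² / 0.64 + 2.394² / 4 = 34.12, so 35 per group. The exact t calculation also gives 35, and the plain normal formula 33. Dividing by 0.85 for dropout gives 39 to 42 per group, or 78 to 84 in total, against 60 planned.

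**5. If all three must succeed.** Each test stays at 5%. By normal approximation with d = 0.8 on every scale and 26 per group, the chance of three successes is about 56% at correlation 0, 65% at 0.5 and 75% at 0.9.

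**The case against.** **Multiplicity belongs in an analysis plan that is not shown, and the article states a per-test level, not a familywise guarantee.** Both observations are fair. But the article itself fixes the three primaries, the threshold and a one-test sample size. A later plan could repair the error rate by dividing alpha, but then the 80% printed here would no longer be true for each outcome.

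**The scales overlap, so 14.3% is an upper figure.** This stands. Independence is unlikely for two cognitive screens with shared domains, and the range should be quoted. Even at a correlation of 0.9 the error is about 8.4%.

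**The 66% is a pessimistic measure of power.** In part. It applies to each outcome at the Bonferroni level. If all three effects truly equal 0.8, the chance of at least one success under Bonferroni is, by normal approximation, about 97% at correlation 0 and 78% at 0.9. Holm raises average power per outcome at 26 per group to about 72% to 76%, still below 80%.

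**A stronger reading: the MMSE is unfit as a primary outcome.** A reader might infer this from the cut-off ("A total score of 23 or below indicates cognitive impairment, whereas a score of 24 or above is considered within the normal range") and the exclusion of preexisting impairment, concluding that baseline scores lie near 30 and that the scale misses what is trained. The documents do not support it.

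- The inclusion criteria require grade I or II cognitive impairment, so near-maximum baselines are not established. No MMSE mean or SD is given.
- The MMSE domains include attention and calculation, recall and language, and Table 2 trains recall, calculation, naming and attention.
- Processing speed is also absent from the list under the Montreal heading ("It assesses various domains of cognition, including visuospatial skills, executive functions, attention, concentration, calculation, language, abstraction, memory, and orientation"). That section opens by naming the MMSE, so even the ownership of the list is unclear.

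**Conclusion.** The point holds: three unranked primary outcomes at 5% each do not match a sample size for one unnamed 5% test. If any one success counts, familywise error is between about 8.4% (correlation 0.9) and 14.3% (independence). Under Bonferroni, power per outcome at d = 0.8 is about 66% at the planned 26 evaluable per group and 73.5% if all 30 are retained. A rule that all three must succeed, which the article does not state, would also fall below 80% at 26 per group.

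The error figures assume equally correlated normal statistics, and the power figures assume d = 0.8 on the outcome or outcomes concerned. Repeated assessments could add further tests and are not counted. The size is not short for every design: with one named primary outcome, the stated 5% and 80% both stand at 60 participants.

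**What to change.** Issue a dated amendment, with its reason, before outcome data are analysed.

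1. **Name one primary outcome at one time point.** The Montreal Cognitive Assessment total score after the intervention is one example, not the only sound choice, and any one of the three scales cures the multiplicity. If it is chosen, confirm that a baseline is collected: Selection of Participants places the MMSE before chemotherapy and the Montreal scale only afterwards, over four cycles. The time point must be explicit, because Trial Design and Participant Timeline assess at 4 weeks, while Selection of Participants adds assessments after each cycle and weekly for 4 weeks.
2. **Tie d = 0.8 to that outcome** in the sample size sections.
3. **Make the other two scales secondary**, tested in a fixed order after the primary or reported without a confirmatory claim.

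If all three must stay primary, use Holm and restate the power: about 66% per outcome at the Bonferroni level with 26 per group.

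Naming one primary needs no additional participants. This matters because the Results section reports 60 already enrolled, whereas restoring 80% per outcome under Bonferroni would take 78 to 84. The cost is a documented change to the primary outcome set of a registered trial, and the other two scales can no longer carry the claim alone.
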